#### Anthropometry/body composition

Various measures of body composition will be taken. Stature and mass will be assessed to the nearest 0.1 cm and 0.1 kg respectively and used to calculate body mass index (BMI). Waist and hip circumference will be measured to the nearest 0.1 cm using standard approaches. Body fat percentage will be calculated using the sum of four skinfolds (triceps, biceps, suprailliac and subscapular) [58]. Skin-fold thickness will be measured to the nearest 0.1 mm using Harpenden callipers (Baty International, West Sussex, UK). The same researcher will perform the measurement of skinfold thickness and the measurements will be taken after an overnight fast. Measurements will be taken twice and an average of the two values recorded unless the second measure is not within 5% of the first skinfold measure, then a third measure will be taken, with the median value then being recorded. Skinfold sites will also be measured in succession. Skinfold measurements will not be taken if the participant reports having recently exercised, been in the sauna, been swimming or has showered (less than 2 h since).

#### Cardiovascular health measures

##### Brachial blood pressure

Resting brachial blood pressure (BP) will be measured prior to any testing or exercise after a five-minute rest period. The average of two measurements will be taken with an automated BP monitor (SpaceLabs, Redmond, WA). If the first two measures for either the systolic or diastolic blood pressures differ by more than 5 mmHg, a third measurement will be taken to determine the mean blood pressure.

##### Central blood pressure and arterial stiffness

Pulse wave velocity (PWV), aortic reflected wave index, central aortic BP and its determinants (reflected and forward wave pressures) will be determined using commercially available hardware and software. After resting for 15 min in the supine position, the radial waveform will be recorded by applanation tonometry. A high-fidelity SPC-301 micromanometer (Millar Instrument, Inc., Houston, Texas), interfaced with a computer utilizing SphygmoCor software, version 9.0 (AtCor Medical Pty. Ltd., West Ryde, New South Wales, Australia) will be employed. The waveform will be calibrated by auscultatory measurement of the brachial BP. From the radial pressure waveform signal the SphygmoCor software calculates the aortic pressure waveform by means of a validated generalized transfer function. Aortic pulse pressure and central to brachial pulse pressure amplification ratio (PPamp) will be calculated. The magnitude of the forward and reflected wave components of the aortic pressure waveform will be determined by wave separation analysis using a modified triangular waveform (SphymoCor software). Aortic PWV will be measured by sequential recordings of the arterial pressure waveform at the carotid and the femoral arteries. Aortic PWV will be calculated as the ratio of the distance in meters to the transit time in seconds.

##### Echocardiography

Echocardiographic measurements will be performed using an ultrasound (Acuson S2000, Siemens Healthcare GmbH, Germany) with the participant in the partial left decubitus position. Left ventricular (LV) dimensions will be determined using two-dimensional directed M-mode echocardiography in the short axis view and these recordings will be analysed according to the American Society of Echocardiography convention. M-mode images will be obtained perpendicular to the posterior wall and as close to the mitral leaflet as possible without images of the mitral leaflet appearing. The interventricular septal wall thickness (IVS), posterior wall thickness (PWT) and internal dimensions of the left ventricle will all be measured at both end diastole and end systole. Left ventricular diastolic function will be assessed using pulsed wave Doppler by assessing the mitral inflow at rest in the apical four chamber view. Pulse wave Doppler recordings of transmitral velocity will be obtained during early (E) and late (atrial-A) periods of left ventricular diastolic inflow, and expressed as the E/A ratio. Tissue Doppler imaging (TDI) will be used to measure the motion of the mitral valve annulus in the apical four-chamber view. The peak relaxation velocities during early (e’) and late (atrial) (a’) diastole will be obtained. Measures of left ventricular diastolic function will be expressed as the E/e’ ratio and the ratio of early to late mitral annular velocity (e’/a’). Cardiac systolic function will also be assessed by using two-dimensional speckle tracking derived myocardial deformation (strain and strain rate). Speckle tracking analysis will be performed on parasternal short axis images for circumferential strain and apical four chamber images for longitudinal strain. Peak strain and peak strain rate will be recorded.

#### Cardiometabolic biomarkers of health

After an overnight fast, 15 millilitres of blood will be obtained from the antecubital vein. Blood samples will be centrifuged, and plasma and serum will be stored at − 80 °C for later analysis. A blood sample via fingerprick will be also be analysed using a Point-Of-Care analyser (CardioCheck Plus, PTS diagnostics, Indianapolis, USA) for, total cholesterol, high-density lipoprotein (HDL) cholesterol, low-density lipoprotein (LDL) cholesterol and triglycerides (TGs). Using the stored plasma and serum samples, the concentrations of various inflammatory markers and markers of metabolic and cardiovascular health will be determined. ELISA tests (Quantikine® HS, R & D Systems, Inc., Minneapolis, MS, USA) will be used to determine the concentrations of glucose, insulin, interleukin-6 (IL-6), high sensitivity C-reactive protein (hs-CRP), as well as adipokines, including adiponectin, leptin, and chemerin. Endothelial dysfunction will be determined by means of measuring circulating adhesion molecules including ICAM-1, VCAM-1 and E-selectin also using commercial ELISA kits. Insulin sensitivity will be estimated using the homeostasis model assessment of insulin resistance (HOMA-IR) [59].

### Statistical analysis

Data will be analysed using Stata (version 15.1, StataCorp LLC, TX, USA). Data will be expressed as mean (SD) or as median (IQR). Data will be tested for normality (Shapiro-Wilks test) and relevant parametric or non-parametric tests will be applied to the testing of hypotheses. Patient characteristics will be reported for all those recruited into the study as well as those remaining in the study at the end of the intervention using descriptive statistics (mean and standard deviation or median and interquartile range or percentages). A linear mixed model analysis will be used to determine the effects of the HIIT intervention on body composition measures and cardiometabolic parameters with fixed factors of exercise group and time and a random factor of participant. The variance-covariance structures will be selected based on Bayes Information Criterion and the unstructured variance-covariance used. In the case of data that is not normally distributed a generalised linear mixed model will be used. Secondary outcome data between the four groups of women will be analysed in a similar way. Participant age and baseline physical activity level will be included in the models as covariates. Statistical significance will be set at 0.05 and effect sizes will also be reported.

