#### Sample size determination

Based on a small effect size of 0.20 (Cohen’s f) for an improvement in relative VO_2_peak after HIIT versus no HIIT [42], performing a priori sample size calculation for a repeated measures analysis of variance with an expected correlation of 0.50 between measurements, alpha of 0.05 and 85% power of detection, a total sample size of 60 women will be required (G*Power, version 3.1.9.2). The sample size will be doubled to account for further planned analysis of secondary outcomes in sub-groups of normal and high BMI women (HIIT normal BMI, HIIT high BMI, CON normal BMI, CON high BMI). The target sample size will be therefore be 120 women exclusive of drop outs.

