### Outcome measures

The primary outcome of the trial is a change in cardiorespiratory fitness after the 14-week HIIT intervention. Secondary outcomes are changes in body composition, cardiovascular health and metabolic biomarkers of health, as well as measures of feasibility and physical activity and sedentary behaviour levels. Both primary and secondary outcomes will be measured before and after the 14-week intervention (Fig. 2).

Table 1 summarises the outcome measures to be made and the time points at which they will be measured during the study.

**Table 1 Tab1:** Indication of physiological variables measured and timepoints of each measurement

Variable	Timepoints measured
*Primary outcome*	
Peak VO_2_, HR at peak VO_2_, HR at 65 and 85% peak VO_2_	Baseline, post-intervention
*Secondary outcomes*	
Anthropometry	
Skinfolds	Baseline, post-intervention
Body mass and waist:hip	Baseline, every 4 weeks during intervention, post-intervention
Brachial blood pressure	Baseline, post-intervention
Central blood pressure and arterial stiffness	Baseline, post-intervention
Echocardiography	Baseline, post-intervention
Biomarkers of metabolic and cardiovascular health	Baseline, post-intervention
Feasibility (adherence and dropout rate)	Baseline, every 4 weeks during intervention, post-intervention
Accelerometry	Baseline, every 4 weeks during intervention, post-intervention

*VO*_*2*_*peak* Peak oxygen consumption, *HR* Heart rate

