#### Randomisation

All eligible women will be classified as being in either one of two BMI groups (normal BMI: 20-24.9 kg/m^2^, *n* = 60; high BMI: 25-35 kg/m^2^, *n* = 60). Women will then be randomized into either a control group (CON) or a group that will follow the HIIT protocol (HIIT) resulting in four groups of women: high BMI control (CON-H; *n* = 30), normal BMI control (CON-N; n = 30), high BMI HIIT (HIIT-H; n = 30) and normal BMI HIIT (HIIT-N; n = 30). The randomisation procedure for the intervention groups will be done using Microsoft Excel RANDBETWEEN function. The RANDBETWEEN function (=RANDBETWEEN (1,2)) is able to assign participants into one of the two groups, in this instance 1 = CON and 2 = HIIT. Two random sequences of 120 numbers each (group 1 or 2) is generated for each BMI category (high and normal). The sequences were generated by an investigator who is not involved in the data collection procedures. Upon enrolment of a participant into the study, the group allocation of the participant is revealed to a non-blinded research assistant responsible for data collection.

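### A Shapiro-Wilk test on the data, not on residuals, chooses the hypothesis test, conflicts with the GLMM rule in the same section, and may be the only rule that reaches VO2peak

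*Protocol article*

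**What the plan says.** All the relevant rules stand in the Statistical analysis section of the protocol article.

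- **The switch:** "Data will be tested for normality (Shapiro-Wilks test) and relevant parametric or non-parametric tests will be applied to the testing of hypotheses".
- **The main model:** "A linear mixed model analysis will be used to determine the effects of the HIIT intervention on body composition measures and cardiometabolic parameters". Its fixed factors are exercise group and time, and participant is random. No group-by-time term is written out.
- **The second rule for non-normal data:** "In the case of data that is not normally distributed a generalised linear mixed model will be used".
- **Covariates:** "Participant age and baseline physical activity level will be included in the models as covariates".

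Three other sections bear on these rules. Outcome measures states: "The primary outcome of the trial is a change in cardiorespiratory fitness after the 14-week HIIT intervention". Cardiometabolic biomarkers of health lists, among others, "interleukin-6 (IL-6), high sensitivity C-reactive protein (hs-CRP), as well as adipokines, including adiponectin, leptin, and chemerin". Randomisation describes two BMI strata of 60 women each: "All eligible women will be classified as being in either one of two BMI groups".

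**The concern.** There are three faults in what the section states.

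1. **The wrong object is tested.** A linear mixed model assumes roughly normal residuals and random effects. It does not assume normal raw values. A preliminary test on the data neither confirms nor refutes that assumption, yet its p-value decides the analysis.
2. **One trigger has two consequences.** Non-normal data go to a non-parametric test under one sentence and to a generalised linear mixed model under another. The analyst has to choose, outcome by outcome, after seeing the data.
3. **The primary outcome may fall under the switch alone.** The mixed-model sentence covers body composition and cardiometabolic parameters. Elsewhere the protocol keeps cardiorespiratory fitness apart from both.

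At stake is whether the analysis is fixed before the data are seen, whether the promised covariates and participant factor are used, and some power for the skewed secondary markers.

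**Working it through.** **Step 1. The plan's own figure.** Sample size determination gives a total of 60 for a repeated measures ANOVA ("Based on a small effect size of 0.20 (Cohen’s f) for an improvement in relative VO_2_peak after HIIT versus no HIIT"; correlation 0.50, alpha 0.05, power 85%). For the within-between interaction with two groups and m = 2 times, λ = f²·N·m/(1−ρ) = 0.04·N·2/0.5 = 0.16N, on 1 and N−2 degrees of freedom.

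- N = 58: λ = 9.28, power 0.849
- N = 59: λ = 9.44, power 0.856
- N = 60: λ = 9.60, power 0.861

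The smallest N is 59, or 60 for equal arms, so the figure reproduces. The between-factor test would need 171. The trial was therefore sized on a group-by-time test, although the analysis text writes out no such term.

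**Step 2. The two rules side by side.**

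| Finding on the data | Normality-test sentence | Mixed-model sentences |
|---|---|---|
| Normal | Parametric test | Linear mixed model |
| Not normal | Non-parametric test | GLMM |
| Outcomes covered | Hypothesis tests in general | Body composition and cardiometabolic parameters; four-group secondary outcomes analysed similarly |

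No rule decides between the columns. Cardiorespiratory fitness is named only by implication, in the first.

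**Step 3. How often the switch fires.** The protocol gives no distributions, so the shapes are assumptions. Shapiro-Wilk rejection at 0.05 in simulated samples of 120:

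| Assumed shape | Rejected |
|---|---|
| Log-normal, log SD 0.3 / 0.5 / 0.8 | 93% / 100% / 100% |
| Two normal strata, gap 1 or 1.5 SD | 5% |
| Two normal strata, gap 2 / 2.5 / 3 SD | 14% / 42% / 82% |

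Skewed markers trip the test almost always. The two-stratum design by itself seldom does unless the strata lie far apart.

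**Step 4. What the non-parametric route costs.** Assumptions: log-normal marker with log SD 0.8, 60 women per arm, effect 0.4 SD on the log scale, no stratum gap, complete data, two-sided 0.05. With two time points and complete data, the group-by-time test equals a t-test on change.

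| Analysis | Power, ρ = 0.5 | Power, ρ = 0.7 |
|---|---|---|
| Log-scale, baseline-adjusted | 0.70 | 0.87 |
| Log-scale group-by-time | 0.59 | 0.81 |
| Mann-Whitney on change | 0.55 | 0.76 |
| Mann-Whitney on post values | 0.55 | 0.56 |

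Differences in points:

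- Against group-by-time, the rank test on change loses 59−55 = 4 and 81−76 = 5.
- Against group-by-time, the rank test on post values loses 59−55 = 4 and 81−56 = 25.
- Against the baseline-adjusted model, the losses are 70−55 = 15 (both rank tests) at ρ = 0.5, and 87−76 = 11 (change) and 87−56 = 31 (post) at ρ = 0.7. That is about 10 to 30.

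**Step 5. Dependence on the effect size.** The 0.4 SD is not the plan's planning effect. In Step 1, λ = 9.6 with 30 per arm equals 15·δ²/[2(1−ρ)] = 15·δ², so δ = √0.64 = 0.8 SD difference in change. At that effect and N = 120, λ = 19.2 and the group-by-time power is 0.99. A repeat of the Step 4 simulation at 0.8 SD put both rank tests at about 0.99 or higher. The power loss therefore concerns moderate effects on secondary markers.

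**The case against.** **The GLMM sentence keeps skewed outcomes in a mixed model.** It directly follows the mixed-model text, and the normality sentence sits among descriptive statistics, so the latter could be meant for simple comparisons only. This stands in part: a reader might infer that non-normal outcomes necessarily leave the mixed model, and the text does not say so. But the normality sentence expressly concerns the testing of hypotheses, so the conflict remains.

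**Stratified recruitment does not in itself make the data non-normal.** A reader might infer this from the two BMI strata. BMI itself would be rejected nearly always (if uniform within strata), but it is the stratifier and is not listed in Table 1. For outcomes that are normal within strata, Step 3 shows rejection of about 5% up to a gap of 1.5 SD. The objection stands.

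**Most of the power is not lost.** A figure as low as 14% can be produced with strata 2 SD apart, correlation 0.8, an effect of 0.33 SD and a rank test on post values only. The plan names no such test, and the switch fires there in only about 12% of trials. Following the two-stage rule gives 73% to 80%, against 80% for group-by-time. The objection stands.

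**Rank tests are not weaker than every model.** On skewed data Mann-Whitney on change matches a raw-scale baseline-adjusted model (0.56 against 0.54 at ρ = 0.5). This stands: the gain comes from prespecifying a suitable scale.

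**Details belong in the full plan.** An unnamed GLMM family alone would be no finding in an article. The point here is different: the article states a rule that tests the wrong object and contradicts its neighbour.

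**Conclusion.** The point holds as a flaw in a stated rule. The section tests data instead of residuals, lets the result select the hypothesis test, and gives two incompatible routes for non-normal data. Because the mixed-model sentence omits cardiorespiratory fitness, the switch may be the only rule that reaches the primary outcome; the text does not settle this.

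The practical effect falls mainly on right-skewed markers such as hs-CRP, IL-6, insulin, HOMA-IR, leptin and triglycerides. If these are log-normal, the test fires in about 93% to 100% of samples of 120. If the non-parametric route is then taken, an ordinary rank test drops the participant factor and the age and activity covariates. Its power is lower by the 4 to 25 points (against log-scale group-by-time) or roughly 10 to 30 points (against a baseline-adjusted log-scale model) shown above.

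These sizes rest on an assumed log-normal shape, log SD 0.8, an effect of 0.4 SD, correlations of 0.5 and 0.7 and no stratum gap. They shrink to almost nothing for an effect as large as the one used in planning. The conflict between the two rules rests on no assumption. The change should be made, but the flaw does not threaten the trial.

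**What to change.** Replace the normality-test sentence and the GLMM sentence with one rule:

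- Use one linear mixed model, fixed in advance, for every continuous outcome. Name VO2peak in it. Include group, time, an explicit group-by-time term, participant as random factor, and the stated age and baseline activity covariates.
- Judge fit on residual plots. No preliminary test chooses the analysis.
- Analyse right-skewed positive markers on the log scale and report ratios of geometric means, or use a GLMM with named family and link, for example gamma with log link. Either is sound; the choice is made per marker before the data are seen.
- Keep rank or permutation tests as sensitivity analyses only.

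This takes a few sentences in the analysis text and needs no extra data, participants or measurements. Since recruitment is under way, the change should be dated and made before the analysis data are examined.

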We acknowledge that a potential limitation, as previously reported [48], will be compliance to the intervention. However, we aim to improve compliance by sending mobile text messages to the participants encouraging them to maintain engagement with the intervention. Motivational messaging is a strategy that has been used in other remote interventional trials [63–65] that have used behavioural therapy (motivation and counselling) which is complementary to exercise prescription. Another limitation to the study is that due to financial constraints it is not possible to provide a heart rate monitor to each participant for the monitoring of heart rate during the exercise sessions for the duration of the study. However, the first HIIT session will be conducted in the laboratory along with an exercise physiologist who will explain the protocol and indicate the individualised RPE at which the participants should exercise throughout the study. RPE using the Borg scale is a valid method for monitoring and prescribing exercise intensity regardless of sex, age, exercise modality or physical activity status [54].

The present study has the potential to inform future research on prescribing exercise therapy for people who are time-constrained. HIIT allows people to be flexible with engaging in physical activity instead of it becoming a burden to perform; and may encourage individuals who do not meet the physical activity guidelines to adopt a low-volume home-based HIIT programme for increasing engagement in physical activity levels for improved cardiometabolic and overall health. In addition, in comparing effects of HIIT between high and normal BMI groups, the current study will possibly identify future areas of mechanistic research as to how home-based own-body weight HIIT confers benefits to cardiometabolic health. The feasibility of low-volume, high-intensity exercise in overweight women could potentially mitigate some of the barriers to performing physical activity in a population that is at risk of cardiometabolic disease. Since HIIT is an effective exercise modality for the maintenance of cardiometabolic health, investigating the adherence to a home-based protocol is an important factor in understanding whether engagement in HIIT is in fact sustainable beyond the laboratory.

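### The mixed model is described without a group-by-time term or adjustment for baseline outcome, and it is assigned to secondary outcomes only, so the primary outcome, VO2peak, has no stated model

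*Protocol article*

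**What the plan says.** **Primary outcome.** Under Outcome measures: "The primary outcome of the trial is a change in cardiorespiratory fitness after the 14-week HIIT intervention". Table 1 lists peak VO2 at baseline and post-intervention only. The same section places the other domains lower: "Secondary outcomes are changes in body composition, cardiovascular health and metabolic biomarkers of health".

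**Model.** Under Statistical analysis, the terms of the linear mixed model are given as follows: "with fixed factors of exercise group and time and a random factor of participant". The outcomes it is assigned to are body composition and cardiometabolic parameters. On covariates: "Participant age and baseline physical activity level will be included in the models as covariates". The baseline value of the outcome is not among them. On covariance: "The variance-covariance structures will be selected based on Bayes Information Criterion and the unstructured variance-covariance used".

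**BMI groups.** "Secondary outcome data between the four groups of women will be analysed in a similar way". The Discussion expects to learn from the trial "in comparing effects of HIIT between high and normal BMI groups".

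**What is absent.** The Statistical analysis section mentions neither cardiorespiratory fitness nor VO2peak. Apart from the mixed model it offers only a general statement that parametric or non-parametric tests will be chosen after a normality check. VO2peak is linked to a method in one place, the repeated measures ANOVA under Sample size determination.

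**The concern.** In a randomised trial with a baseline and a week-14 measurement, the HIIT effect is the between-arm difference at week 14, allowing for baseline. In a repeated-measures model that keeps baseline as an outcome, the group-by-time term carries it. A model with group and time as main effects alone forces the arm difference to be the same before and after the intervention. Randomisation makes the expected baseline difference zero, so the group coefficient mixes a zero with the real effect, and the time coefficient pools the change in both arms. Neither is the HIIT effect.

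Two further points follow. First, the outcome on which the trial is judged has no specified test, so the choice is open until the data are seen. Second, the four-group analysis inherits the missing interaction, and no contrast is named that compares the HIIT effect between BMI strata. The hypothesis under Study objectives speaks of change in the high-BMI women doing HIIT and does not mention their controls, so the text does not settle which comparison would decide it.

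**Working it through.** **Inputs, from Sample size determination:** Cohen's f = 0.20, correlation between measurements ρ = 0.50, α = 0.05, target power 85%, N = 60, doubled to 120. VO2peak has m = 2 visits (Table 1), and there are k = 2 arms.

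**Step 1. Reproduce the plan's 60.** For the group-by-time test in a repeated measures ANOVA the noncentrality is λ = f²·N·m/(1−ρ), with 1 and N−2 degrees of freedom.
- N = 60: λ = 0.04 × 60 × 2 / 0.5 = 9.6, power 86.1%.
- N = 120: λ = 19.2, power 99.1%.

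With equal arms, 60 is the smallest total that reaches 85%, so the stated figure is reproduced. The test of time alone also gives 60, so the figure does not prove which option was selected.

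**Step 2. The only between-arm term in the model as written.** For the group main effect, λ = f²·N·m/(1+(m−1)ρ).
- N = 60: λ = 0.04 × 60 × 2 / 1.5 = 3.2, power 42.1%.
- N = 120: λ = 6.4, power 70.9%.
- 85% power needs N = 172.

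**Step 3. What each coefficient estimates.** Let the arms be equal at baseline and differ by δ at week 14. For the interaction, f = 0.20 means cell effects of ±δ/4 = ±0.2 SD, so δ = 0.8 SD. With equal variances at the two visits, the main-effects model gives
- group coefficient = (0 + δ)/2 = 0.40 SD;
- time coefficient = δ/2 = 0.40 SD when controls do not change.

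The group coefficient of 0.40 SD means group effects of ±0.2 SD, so f = 0.20 applies in step 2 as well. In 4,000 simulated trials at each N, the mean group coefficient was 0.39 to 0.40 SD and the mean interaction 0.80 SD.

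**Step 4. How general is one half?** With an unstructured covariance, visit SDs s₁ and s₂ and correlation ρ, the main-effects group coefficient is w·δ, where

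w = (s₁² − ρs₁s₂)/(s₁² + s₂² − 2ρs₁s₂).

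| ρ (assumed) | s₂/s₁ = 0.8 (assumed) | s₂/s₁ = 1.0 | s₂/s₁ = 1.2 (assumed) |
|---|---|---|---|
| 0.3 | 0.66 | 0.50 | 0.37 |
| 0.5 | 0.71 | 0.50 | 0.32 |
| 0.8 | 1.00 | 0.50 | 0.08 |

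One half holds for two visits with equal variances. Otherwise the coefficient has no fixed relation to the HIIT effect. Body mass and waist:hip are also measured at weeks 4, 8 and 12, so the two-visit result does not carry over to them.

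**Step 5. The baseline-adjusted alternative.** Adjusting week 14 for baseline leaves a residual SD of √(1−ρ²) = √0.75 = 0.866. The standardised effect is 0.8/0.866 = 0.924 and λ = 0.924² × 60/4 = 12.8, giving power of about 94% at N = 60.

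**Step 6. The four-group analysis.** A four-level group factor crossed with time has the same mean structure as HIIT × BMI × time. Effect modification is one contrast in it: (HIIT-H − CON-H) minus (HIIT-N − CON-N), each in terms of change. An overall four-group test does not isolate that contrast, and the article does not name it.

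**The case against.** The strongest reply is that listing the factors of a group-by-time design is common shorthand for a model that includes their interaction, particularly in a condensed article, and that nothing in the text excludes the interaction. Other sections support this. The sample size concerns improvement with HIIT against no HIIT, and its N of 60 fits the interaction but not the group main effect. The Discussion sets out to learn whether changes in each BMI group differ from those in non-exercising controls, which is a difference in change. The wording of the four-group sentence also suggests that the preceding model was meant as the main two-arm analysis, so the omission of VO2peak may be a drafting slip.

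Much of this stands, and it rules out claiming that the trial will report half its effect. It does not remove the point. The section does not defer to another document: it sets out the fixed terms, random term, covariates, covariance and outcomes, and the term that answers the trial's question and the primary outcome are both missing. Fitness cannot be assumed to fall under cardiometabolic parameters, because Study objectives lists the two separately.

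Three further objections succeed:
- The four-group factor is not wrong in itself. With time crossed in and the contrast named, it is equivalent to HIIT × BMI × time.
- The covariance sentence might be taken to describe a model that cannot be fitted, since an unstructured residual covariance plus a participant intercept has four parameters for three moments at two visits. The article does not say that unstructured refers to the residuals, so this is conditional.
- A reader might fear that a gain shared by both arms would pass as benefit through the time term. With an assumed shared gain of 0.3 SD and N = 120, that term has standard error 1/√120 = 0.091 and is significant in about 91% of trials. The gain is an assumption, and nowhere is the time effect named as the efficacy test.

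**Conclusion.** The point holds as a defect of specification. The described model contains no term for the HIIT effect and no adjustment for baseline outcome, and the primary outcome has no stated model. If the model were fitted literally, the between-arm coefficient would be a time-averaged difference: half the week-14 effect (0.40 SD in place of 0.80 SD), with power of 42% at N = 60 and 71% at N = 120, against 86% and 99% for group-by-time. These figures rest on main effects only, two visits, equal variances, ρ = 0.50, f = 0.20 and no dropout.

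A reader might infer that the investigators plan the main-effects analysis or that the sample size is wrong. The documents support neither: 60 is reproduced by the interaction test, and the aims describe a difference in change. The identifiability and shared-gain points are conditional and carry no weight here. What is needed is to bring the written model into line with the sample size section and the stated aims.

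**What to change.** Amend the Statistical analysis section before the data are analysed:

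1. Name relative VO2peak as the outcome of the primary model.
2. Define the HIIT effect as the HIIT-minus-CON difference at week 14. Estimate it either from group-by-time, preferably with the arms' baseline means constrained equal, or from the week-14 value adjusted for its baseline. Apply the same definition to the secondary outcomes.
3. For the BMI analysis, name the contrast that compares the HIIT-minus-CON effect between strata. Report that effect within each stratum with its confidence interval.
4. Test the high-BMI hypothesis as HIIT-H against CON-H, not as change within HIIT-H.
5. State one covariance structure. If it is an unstructured residual covariance, omit the participant random intercept for outcomes measured at two visits.

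The cost is wording only. Recruitment, visits, measurements and the target of 120 are unchanged, and at the plan's own inputs the baseline-adjusted option raises power at N = 60 from about 86% to 94%.
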